### Study design

2.1.

The study is a single-center prospective observational cohort study. Study data combines observations from different sources: patients’ remote self-assessment, data from treating neurologists obtained in routine clinical care—both performed semiannually—and data from annual in-person study visits at an academic clinical research center. The primary outcome consists of home-based recordings of short motor tests (Amsa, Motognosis GmbH, Berlin, Germany) performed twice a day for a period of 1 week every 6 months. Patient-reported outcomes is acquired every 6 months using validated questionnaires on specific functions, impairments and quality of life.

Data requested from treating neurologists comprise the Multiple Sclerosis Functional Composite (MSFC-3) (35), the global assessment of the change since last observation [clinical global impression of change (CGI) (36)] and information on relapse events/relapse therapy including recovery, change of therapy or comorbidity since prior visit.

Annual study visits at the research site comprise clinical and functional assessment including Motognosis Labs as well as imaging of brain (MRI) and retina (OCT) detailed below.

The observation period is 24 months for the primary endpoint with an additional clinical assessment at 27 months to confirm progression defined by EDSS.

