### Data acquisition

2.3.

An overview of the visit schedule is provided in Table 1.

**Table 1 tab1:** Overview study assessments and visit schedule.

Assessment	Rater	Screening	Baseline visit (V) 1	Visit 2	Visit 3	Visit 4	Visit 5	Visit 6
			Month 1	Month 6	Month 12	Month 18	Month 24	Month 27
Written informed consent	Investigator	□						
Assessment of in- and exclusion criteria/confirmation of in and exclusion criteria	Investigator	□	□		□		□	□
Assessment/Follow up of patients’ characteristics (diagnosis ascertainment, comorbidities, age, height, weight, relapses in past 24 months/since last visit, current symptoms, treatment: current treatment at baseline, change of treatment at follow-up)	Investigator		□		□		□	□
EDSS	Investigator	□	□		□		□	□
MSFC-4	Study assistant		□		□		□	□
6-min walk test	Study assistant		□		□		□	□
PASS-MS assessment of motor functions			□		□		□	□
PRO PGIC	Patient		□	●	□	●	□	□
PRO MSWS-12	Patient		□	●	□	●	□	□
PRO FSMC	Patient		□	●	□	●	□	□
PRO NRS	Patient		□	●	□	●	□	□
PRO HAQUAMS	Patient		□	●	□	●	□	□
PRO PHQ-9	Patient		□	●	□	●	□	□
PRO GLTEQ	Patient		□	●	□	●	□	□
PRO EQ-5D-5L	Patient		□	●	□	●	□	□
PRO BPI	Patient		□	●	□	●	□	□
Instruction (Reinstruction if needed) of use for Amsa	Study assistant		□	(●)	(□)	(●)	(□)	
Amsa assessment recorded twice a day over 7 days	Patient		●	●	●	●	●	
Reporting of AE and safety issues related to Amsa self-assessment	Patient		●	●	●	●	●	
PRO Pain-NAS, EQ-VAS, state fatigue once a day on each day of functional assessment	Patient		●	●	●	●	●	
Usability rating	Patient		●	●	●	●	●	
Brain MRI			□				□	
OCT			□				□	
Clinical global impression of change	Treating neurologist			◊	◊	◊	◊	◊
Most recent relapse incl treatment and course of remission	Treating neurologist		◊	◊	◊	◊	◊	◊
Current medication/Change in medication from baseline/comorbidities	Treating neurologist		◊	◊	◊	◊	◊	◊
MSFC-3	Treating neurologist		◊	◊	◊	◊	◊	◊

The components of each visit are denoted as (□) annual research grade assessment at study center, (●) remote self-assessment of motor functions at home (Amsa) and (◊) clinical data collected from routine visits.

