#### Primary outcome: self-assessment of motor functions at home (Motognosis Amsa)

2.3.1.

Measurements are recorded with a markerless motion analysis system consisting of the measurement software (Amsa V 1.2.0, Motognosis GmbH, Berlin, Germany) running on an All-in-One PC (Optiplex 5,480, Dell GmbH, Frankfurt am Main, Germany) and a single RGB-Depth camera (Azure Kinect, Microsoft Corporation, Redmond, WA, United States).

The device is delivered to the patient’s home and set-up appropriately by qualified staff along with oral instruction of the testing protocol which includes assessment of six specified short motor tasks within the recording space of the camera. All data are stored on the system hardware only.

Participants are instructed to use Motognosis Amsa twice a day—preferably morning and later afternoon/evening—for a period of 7 days for each visit. Participants start by preparing the measuring area (e.g., removal of clutter). When the measurement area is cleared, they can start the software. The software can be controlled with gestures, i.e., lifting of the left or right arm. Assessments start with a positioning phase, where participants will see themselves on the computer screen and will be guided to the correct starting location with visual and auditory cues. Subsequently assessment-specific video instructions are provided. After execution of an assessment a result page is shown. If a measurement error occurred, a notification will be shown with the request to rerecord. Otherwise, the participant can proceed to the next assessment. If a specific task was not recorded, the participant is supposed to enter the reason for the omission in a free text field.

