### Pre-processing of data

2.4.

All study data will undergo plausibility checks including description of missings prior to further analysis. Definitions of progression events by EDSS or alternative definitions for secondary outcomes are applied as provided in section 2.3.

Data from technical recordings (Amsa, Motognosis Labs, MRI, and OCT) are continuously monitored by trained users to check usability and plausibility according to standard operating procedures for quality control (QC). Specifically, for Amsa and PASS-MS, presentations of all assessments are systematically inspected and evaluated for quality concerns following the QC pipeline developed by Röhling et al. (70).

For RGB-D camera based motion capture, both Amsa and PASS-MS, a list of task-specific kinematic parameters is generated according to custom scripts by the provider. Kinematic parameters include for example gait speed for the short walking tasks. Primary analysis will consider only one parameter per test condition, i.e., seven parameters.

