### Statistical analysis plan

2.7.

Based on the study question, the primary hypothesis is to assess the accuracy of detecting disease progression by the repeated short motor assessments at 24 months, compared to progression defined by EDSS at 24 months and confirmed at 27 months.

The sample size is justified via the expected precision of the estimate of the area under the receiver operating characteristic curve (AUC) provided in terms of the 95% confidence interval. We hypothesize that the parameters derived from repeated short motor assessment at home can reliably identify disease progression compared to detection of progression according to EDSS.

If the AUC is 0.9, and the sample size is 150, from which 10% are diagnosed with a progression according to EDSS at 24 months, then the width of the 95% confidence interval will be 0.103. In case of a lower AUC, e.g., 0.8, the 95% confidence interval would be of width 0.138. These calculations were performed using nQuery version 8.7.0.0, procedure AOC6-1. Given these calculations, the expected precision of the estimated quantity seems sufficient to evaluate the exploratory research hypothesis of this study.

Given the baseline definition, the primary endpoint is analyzed as AUC of detection of disease progression according to the repeated short motor assessment at home compared to detection of disease progression according to the EDSS score at 24 months, confirmed at 27 months. The AUC is calculated alongside with the 95% confidence interval. Event of progression at 24 months detected by parameters from repeated short motor assessment at home is defined as observed reliable change in pre-defined direction of worsening in one or more of the parameters derived from this assessment. Threshold for reliable change will be defined based on analysis of baseline data. Secondary endpoint analyses are planned for MSWS-12, HAQUAMS, PGIC, CGI, MSFC, and 6 MW. Respective receiver operating characteristic curves and their AUC will be calculated based on published evidence on minimally important difference for MSFC, 6 MW, MSWS-12, and HAQUAMS while any transition in the direction of worsening will be considered an important change on PGIC and CGI.

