The technical approach applied in this study is novel in two aspects: first, assessments of motor function are recorded by patients themselves in their home setting, and second, this approach enables frequent (multi-point) assessment. Both aspects hold potential to overcome the limitations of conventional rater-based assessments in single and infrequent clinical visits. Previous evidence suggests that different features of MS may vary considerably within the same subject, including self-ratings of health status (83). For fatigue, over one-third of the variability can be attributed to moment-dependent fluctuations, 8.2% to day-to-day fluctuations, while 56.6% can be attributed to individual differences (84) and many pwMS report increased fatigue in the afternoon and evening (85). Day-to-day variability has also been shown for maximum walking distance that would equal changes of up to 1.5 EDSS points (86). We therefore expect to observe day-to-day variability of motor performance throughout each week of remote assessment and consider this in definitions of change at follow-up. Further, our study protocol combines repeated self-recording of motor functions with a daily self-report of health status, pain and state fatigue. This will allow us to study possible correlates.

For a quantitative assessment of motor functions in MS, this study follows the technical approach of a task-based assessment. Clinical relevance of instrumentally assessed gait quality has been shown in early-stage multiple sclerosis (87). However, their ecological validity may be limited, depending on task and setting (88).

Shema-Shiratzky et al. found that dual-task walking in the lab better represents walking ability in everyday life, whereas usual walking in the lab is more likely to represent best performance in everyday life (89).

We therefore included additional performance-based and patient-reported outcomes of walking function for contextualization. Another novelty of our study is the integration of data acquired semiannually in the course of routine clinical care by treating neurologists. Analysis will use these, specifically their global ratings of change, as one of the alternative secondary definitions of change. This intends to explore the validity and generalizability of our findings for the setting, in which approved treatments or digital motor applications will ultimately be applied.

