We aimed to address potential drawbacks of remote task-based assessment in study design and analysis plan. First, variability in task performance can be expected to be higher in unsupervised settings. We aim to mitigate this point by control of device set-up by a trained operator, standardized instructions and by technical design. Second, we apply a standardized quality control pipeline on recordings to identify relevant protocol deviations. Roehling et al. showed the feasibility but also the necessity for a *post hoc* quality control using this method of instrumented motion analysis (70). In this study, we extend this QC pipeline exploring its practicality to Amsa measurements. Furthermore, participants’ adherence is surely a concern in this long-term observation. A recent 8-week RCT study investigated participants’ short term adherence in using digital tools in multiple sclerosis. The average overall adherence for all three measurement tools (1. MS patient-reported outcome tool accessible via a smartphone app, 2. Floodlight open, a app-based assessment of hand and gait function, and 3. Fitbit, a smart watch for passive monitoring of sleep duration and quality) was 81% in the intervention group (90). Midaglia et al. analyzed the practicability of remote active testing and passive monitoring using digital tools in pwMS and showed 70% (16.68/24 weeks) adherence to active testing and 79% (18.89/24 weeks) to passive monitoring (74). Rates of attrition in application of remote assessment have not yet been reported over longer time-frames. In order to sustain adherence in our 24 months-study, participants will receive a reminder link about 4 weeks before the upcoming measurement and the Amsa device will be delivered by the study team at the appropriate time.

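### The reliable-change threshold comes from baseline data only, which cannot show week-to-week or re-installation variance, so the false-positive rate of the one-or-more-of-seven rule is uncontrolled

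*Protocol article*

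**What the plan says.** Section 2.7 (Statistical analysis plan) defines the home-test progression event at 24 months as "observed reliable change in pre-defined direction of worsening in one or more of the parameters derived from this assessment". It then names where the cut-off comes from: "Threshold for reliable change will be defined based on analysis of baseline data". No other data source, formula, confidence level or summary measure (weekly mean or single recording) is given. Section 2.4 (Pre-processing of data) sets the number of parameters: "Primary analysis will consider only one parameter per test condition, i.e., seven parameters".

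On the measurements, section 2.1 (Study design) has the tests "performed twice a day for a period of 1 week every 6 months", and Table 1 shows one such period at baseline and none at screening ("Amsa assessment recorded twice a day over 7 days"). Section 2.3.1 has the device brought to the home and "set-up appropriately by qualified staff along with oral instruction of the testing protocol". Section 2.5 (Data management) has it retrieved after each one-week period. For later periods, the Discussion says "the Amsa device will be delivered by the study team at the appropriate time".

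The Discussion also indicates which noise the authors have in mind. They expect day-to-day variability "throughout each week of remote assessment and consider this in definitions of change at follow-up". Variability from one week to another is not mentioned.

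**The concern.** A reliable-change threshold should mark the change that measurement error and ordinary fluctuation would rarely produce in someone who is stable. The change judged here is month 24 minus baseline. It therefore carries within-week noise and also whatever shifts a person's whole week: the camera's new position, the room, practice, and general condition in that week.

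With one week and one installation per participant, those week-level shifts cannot be separated from differences between people. Baseline data can give the day-to-day and time-of-day components, but not the week-level component. Averaging up to 14 recordings shrinks the first kind of noise and leaves the second untouched.

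The resulting yes/no event is the index classification of the primary endpoint. Because worsening on any one of seven parameters is enough, a per-parameter error is compounded.

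**Working it through.** **The plan's own figure.** None is stated for the threshold, its error rate or any variance component, so there is nothing to reproduce. The only design figures in section 2.7 concern the precision of the AUC and do not bear on this point.

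**Inputs from the article.**
- Recordings per period: 2 per day × 7 days = up to 14 (Table 1).
- Parameters: 7 (section 2.4).
- Rule: worsening in at least one (section 2.7).
- Expected non-progressors: 150 × 0.90 = 135 (section 2.7).

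**Assumptions, not in the article.**
- Normal errors and a one-sided flag for worsening.
- A multiplier of 1.96.
- τ, the combined between-week and re-installation SD as a fraction of the within-week single-recording SD (SDw), set at 0, 0.25 or 0.5.
- Correlation between parameters of 0 or 0.5.

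**True variance of a stable participant's change in weekly mean:** 2·SDw²·(1/14 + τ²).

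**Case A: threshold built on the precision of the weekly mean.** Threshold = 1.96·√2·SDw/√14. The true SD of change exceeds the assumed one by the factor f = √((τ² + 1/14)/(1/14)) = √(1 + 14τ²). The per-parameter false-positive rate is p = P(Z > 1.96/f). Any-of-seven is 1 − (1 − p)⁷ if independent, and is simulated at correlation 0.5.

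| τ | f | p | any of 7, correlation 0.5 | any of 7, independent | of 135 stable |
|---|---|---|---|---|---|
| 0 | 1.00 | 2.5% | 12% | 16% | 16–22 |
| 0.25 | √1.875 = 1.37 | 7.6% | 28% | 43% | 38–57 |
| 0.5 | √4.5 = 2.12 | 17.8% | 51% | 75% | 69–101 |

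The τ = 0 row matters. Even a correctly scaled threshold flags 12–16% through the any-of-seven rule, so the excess is the difference from that row.

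**Case B: threshold built on single-recording variability, applied to weekly means.** Threshold = 1.96·√2·SDw, so p = P(Z > 1.96/√(1/14 + τ²)).
- τ = 0.25: p is about 4 × 10⁻⁸ and any-of-seven is practically zero.
- τ = 0.5: p is about 0.03% and any-of-seven (independent) about 0.2%.
- p reaches 2.5% only when 1/14 + τ² = 1, that is τ² = 13/14 ≈ 0.93.

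This threshold is √14 ≈ 3.7 times as wide as in Case A. It avoids false positives at these ratios, but true worsening must be much larger to register.

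**Effect on the AUC.** For a yes/no index event, AUC = (sensitivity + specificity)/2. A narrow threshold lowers specificity and raises sensitivity. The comparison below sets a correctly scaled threshold against one too narrow by 1.37. It is simulated at correlation 0.5, with all seven parameters shifted in progressors by the stated number of SDs of change (an assumption):
- 0.5 SD: 0.578 to 0.614
- 1.0 SD: 0.691 to 0.726
- 1.5 SD: 0.804 to 0.805
- 2.0 SD: 0.885 to 0.843

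With a threshold too narrow by 2.12, the AUC rises at 0.5 SD, is flat at 1.0 SD and falls from 1.5 SD upward.

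**The case against.** The strongest reply is that the harm depends on a formula the article does not state. The same assumed variance ratios give a severe problem in Case A and none in Case B, and the remark in the Discussion about day-to-day variability fits either. Formula detail may properly sit in a document not shown. This stands. A reader might infer that the plan will flag stable patients as progressing; the documents support only that it may.

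A reader might also infer that the AUC is biased downward. The simulation does not support that as a general statement. The direction turns on how large true worsening is, and the Discussion says the study is looking for subtle change.

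The Discussion also lists controls on set-up: a trained operator, standard instructions, technical design and quality control of recordings. Section 2.3.1 adds guided positioning before each task. These should reduce the set-up part of the variance, but they do not measure what remains.

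Finally, fixing a cut-off from baseline data has the merit of independence from follow-up outcomes, and the study calls its hypothesis exploratory. Both points lower the severity. Neither makes the missing component estimable, and the data source is something the article does fix.

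**Conclusion.** The point holds as a limit of the stated data source. One week and one installation per participant cannot supply the week-to-week and re-installation variance present in every month-24 change, so the false-positive rate of the any-of-seven rule is not controlled. This conclusion needs no outside figure.

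The size is conditional. With a weekly-mean threshold and τ of 0.25 to 0.5, any-of-seven false positives are 28–43% to 51–75%, against 12–16% for a correctly scaled threshold. With a single-recording threshold there is no excess below a variance ratio of about 0.93, and the cost falls on sensitivity, with only about 15 progressors expected (150 × 0.10). In either case the threshold is too narrow or too wide by an amount the baseline data cannot reveal. Specificity is affected directly; the sign of the effect on the AUC is not determined. Severity: should be fixed.

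**What to change.** Replace the sentence on the threshold's source with a rule that:

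1. States the weekly summary per parameter, the formula and the confidence level.
2. Estimates the no-change error SD of that summary from between-week data, using baseline-to-month-6 changes with month 12 as a check. Restrict this to participants with no intervening relapse who are stable by criteria independent of the home test. Each later week is also a new installation, so these changes carry both missing components together, which is the sum the threshold needs.
3. Uses a variance-component model (participant, week, day, time of day) or a robust SD of the change. The baseline week then serves the within-week components only.
4. Makes no reference to month-24 or month-27 EDSS and is locked before the month-24 analysis.
5. Reports the baseline-only threshold as a sensitivity analysis.

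The cost is a short amendment and one mixed model. No new data are needed, because Table 1 already schedules the home recordings at months 6 and 12. The downside is that inclusion is enriched for progression, and relapse-free participants can still worsen. Some slow true worsening, including progression independent of relapse, may enter the 6- to 12-month changes and widen the threshold. The stability criteria and a robust SD limit this but do not remove it.

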## Discussion

3.

This study evaluates the concept of remote multipoint assessment of motor performance to improve definitions of disease progression in MS over current definitions of 3 m-CDP. Being among the first and larger studies to evaluate quantitative motor assessments longitudinally (28, 72–76), it is also the first study to apply RGB-D technology for the remote assessment of motor functions in MS (77). The prospective design and multimodal examination protocol ensures that changes defined by remote assessment can be compared with state-of-the-art clinical and imaging endpoints in MS.

Primary analysis will use 3 m-CDP defined by EDSS as the main comparator, which is most commonly used as an endpoint of disability accumulation in MS clinical trials to date. Still, more general concerns have been raised with respect to disability confirmation by EDSS (78). For example, 3 m-CDP may overestimate the accumulation of disability in the longer term and, thus, longer confirmation periods should be preferred (79) which would extend observation times. We here adhere to an observation period of 24 months as the minimum among previous studies that used CDP as their main endpoint. Within this timeframe, reasonable proportions of progression events can be expected according to previous reports. Nonetheless, proportions were not much higher than 10% in earlier disease stages (80–82). Targeting this group for our study has the risk that progression observed is too subtle to yield numbers that could answer the primary research question. Therefore, the inclusion criteria were set to increase the likelihood of disability progression while at the same time maintaining generalizability for early MS.

The technical approach applied in this study is novel in two aspects: first, assessments of motor function are recorded by patients themselves in their home setting, and second, this approach enables frequent (multi-point) assessment. Both aspects hold potential to overcome the limitations of conventional rater-based assessments in single and infrequent clinical visits. Previous evidence suggests that different features of MS may vary considerably within the same subject, including self-ratings of health status (83). For fatigue, over one-third of the variability can be attributed to moment-dependent fluctuations, 8.2% to day-to-day fluctuations, while 56.6% can be attributed to individual differences (84) and many pwMS report increased fatigue in the afternoon and evening (85). Day-to-day variability has also been shown for maximum walking distance that would equal changes of up to 1.5 EDSS points (86). We therefore expect to observe day-to-day variability of motor performance throughout each week of remote assessment and consider this in definitions of change at follow-up. Further, our study protocol combines repeated self-recording of motor functions with a daily self-report of health status, pain and state fatigue. This will allow us to study possible correlates.

For a quantitative assessment of motor functions in MS, this study follows the technical approach of a task-based assessment. Clinical relevance of instrumentally assessed gait quality has been shown in early-stage multiple sclerosis (87). However, their ecological validity may be limited, depending on task and setting (88).

Shema-Shiratzky et al. found that dual-task walking in the lab better represents walking ability in everyday life, whereas usual walking in the lab is more likely to represent best performance in everyday life (89).

We therefore included additional performance-based and patient-reported outcomes of walking function for contextualization. Another novelty of our study is the integration of data acquired semiannually in the course of routine clinical care by treating neurologists. Analysis will use these, specifically their global ratings of change, as one of the alternative secondary definitions of change. This intends to explore the validity and generalizability of our findings for the setting, in which approved treatments or digital motor applications will ultimately be applied.

We aimed to address potential drawbacks of remote task-based assessment in study design and analysis plan. First, variability in task performance can be expected to be higher in unsupervised settings. We aim to mitigate this point by control of device set-up by a trained operator, standardized instructions and by technical design. Second, we apply a standardized quality control pipeline on recordings to identify relevant protocol deviations. Roehling et al. showed the feasibility but also the necessity for a *post hoc* quality control using this method of instrumented motion analysis (70). In this study, we extend this QC pipeline exploring its practicality to Amsa measurements. Furthermore, participants’ adherence is surely a concern in this long-term observation. A recent 8-week RCT study investigated participants’ short term adherence in using digital tools in multiple sclerosis. The average overall adherence for all three measurement tools (1. MS patient-reported outcome tool accessible via a smartphone app, 2. Floodlight open, a app-based assessment of hand and gait function, and 3. Fitbit, a smart watch for passive monitoring of sleep duration and quality) was 81% in the intervention group (90). Midaglia et al. analyzed the practicability of remote active testing and passive monitoring using digital tools in pwMS and showed 70% (16.68/24 weeks) adherence to active testing and 79% (18.89/24 weeks) to passive monitoring (74). Rates of attrition in application of remote assessment have not yet been reported over longer time-frames. In order to sustain adherence in our 24 months-study, participants will receive a reminder link about 4 weeks before the upcoming measurement and the Amsa device will be delivered by the study team at the appropriate time.

Our aim is to evaluate subtle changes in motor signs to identify chronic progression in MS independent of relapse by remote task-based assessment. This new approach will be related to the EDSS as well as imaging surrogates (OCT, MRI). Reliable remote assessment of disability would seamlessly fit in the landscape of digital health solutions that are highly important in situations where specialized care is scarce or episodically unavailable, such as in recent pandemic conditions. If utility can be shown for this home-based setting, such assessment may serve as a valuable source of information in patient care. An appropriate re-definition of progression events may substantially reduce total observation times and rater involvement in clinical trials that aim to establish clinical stability or clinical progression in MS as their outcome of interest.

